#### Clinical-Functional Vulnerability Index (CFVI-20)

In addition to being an eligibility criterion for participants’ inclusion at baseline, the CFVI-20 score is also used to assess the responses to the two training interventions investigated. This questionnaire covers multidimensional aspects of the older adult’s health condition and is a viable tool for screening older individuals at increased risk of frailty [35]. It is divided into eight sections: age, health self-perception, functional disabilities (three instrumental activities of daily living and one activity of daily living), cognition, mood, mobility (reaching, grasping and pinching, aerobic/muscular capacity, gait, and sphincter continence), communication (vision and hearing), and the presence of comorbidities. There are 20 questions, which result in a maximum of 40 points. The higher the score, the greater the risk of clinical-functional vulnerability [34]. In addition, CFVI cut-off values are also applied to classify the level of clinical-functional vulnerability, with scores ranging 0–6, 7–14, and  ≥ 15 points considered as having a low risk, an increased risk, or an installed risk of clinical-functional vulnerability or frailty, respectively [34]. Older individuals with a score  ≥ 7 will be included in this study.

#### Dynamic balance

The TUG test without a simultaneous cognitive task is applied for measuring dynamic balance. As previously explained, participants are asked to sit in a chair with a height of ≈ 46 cm, with their backs against the backrest and their hands on their legs. After receiving the orientation, the participants should get up without using their arms, walk 3 m at their normal pace, turn around, walk back to the chair, and sit down until their backs are in touch with the backrest again [41]. Those older adults who can perform the test in 10 to 20 s are considered independent. However, those who take longer than 20 s to complete the test are possibly in a state of postural instability and at higher risk for falls [38].

#### Handgrip strength

The amount of force produced by a maximal isometric contraction of the extrinsic hand muscles of the dominant upper limb is measured using a hand dynamometer, and handgrip strength is recorded in kgf. The test is performed with the participant seated, with his or her shoulder in a neutral position close to the body and the elbow flexed at 90° without support. Three attempts are provided, and the average value is considered for analysis [23].

#### 30-s Sit-to-Stand test

Lower limb strength is assessed using the 30-s Sit-to-Stand test, which involves counting the number of times the participant can stand up entirely from the sitting position with arms crossed over the chest. The performance is measured based on the total number of times the participant can perform the movement for 30 s [43].

#### World Health Organization Quality of Life-bref (WHOQOL-bref)

The self-reported quality of life is assessed by the WHOQOL-bref questionnaire. It is a 26-item questionnaire covering four domains: physical health, psychological health, social relationships, and environment [54]. The questions must be answered using a Likert scale ranging from 1 (e.g., very dissatisfied) to 5 (e.g., very satisfied). Domain scores for the WHOQOL-BREF are calculated by multiplying the mean of all items in each domain by a factor of four. These scores are then transformed to a 0–100 scale as described in detail elsewhere [56], and higher scores indicate a better self-perceived quality of life [44].

#### Hospital Anxiety and Depression Scale (HADS)

The HADS is an instrument composed of 14 items, seven of which are related to anxiety and seven related to depression, which allows the assessment of symptoms in the previous week. Each HADS item ranges from 0 to 3 points, for a maximum of 21 points in each subscale (i.e., anxiety and depression). This instrument was developed by Zigmond and Snaith [59] and was previously translated and validated for the Brazilian population [13].

#### Canadian Occupational Performance Measure (COPM)

The COPM is a semi-structured interview that uses a typical day as a reference to identify issues in self-care, productivity, and leisure based on the self-reported performance capacity and satisfaction of the patient in occupations the participant needs, wants, and/or is expected to do. Initially, the participant is asked to list the main occupational difficulties he or she encounters in the areas of leisure, productivity, and self-care. The participant then is asked to score each of the issues mentioned from 1 (least important) to 10 (most important). Based on the participant’s list, the five most important occupational performance issues are selected so that the participant can classify their performance and their satisfaction in each specific activity, again using a scale from 1 to 10. The performance scores are summed and divided by the number of issues reported, and the same is done with the satisfaction scores to obtain the COPM result [39].

#### Digit span test (DST)

The DST is used to evaluate working memory. During the test, participants are asked to verbally recall a series of numbers that are said by the researcher. The test begins with three numbers from 0 to 9, which are read with a 1 s interval between each number, and that the participant should recall in the correct order. In case the participant recalls them correctly, a new sequence is provided with an additional digit (i.e., four digits), and so on. The test ends when the participant is not able to recall the correct sequence two times in a row. The higher the number of digits recalled, the better the working memory [48].

#### Verbal fluency test

Participants must name as many animals as they know in 1 min, controlled by the assigned researcher using a stopwatch. Different species and animals that have different names for their male and female versions (e.g., ox and cow) are only counted once. The score is considered the total number of animals recalled during the assigned time and classified according to education-adjusted cut-off points [36]. Because both the Verbal Fluency and Dual-task tests require participants to name different animals, the tests will be performed on separate days to avoid or reduce potential interference.

#### Systemic blood pressure

Resting systolic (SBP) and diastolic (DBP) blood pressure measurements are taken in the sitting position using an automated blood pressure monitor (Omron, HEM-7200, China) according to established guidelines [55]. One measurement is taken on each arm with a 1-min interval, and two additional measurements are taken on the arm that shows the highest blood pressure value. The mean of the three SBP, DBP, and resting HR measurements performed on the same arm will be used for the analysis.

### Medical authorizations

Medical authorizations for the practice of physical exercises are requested for each randomized participant. In addition, adverse events are assessed through the intervention and classified according to severity (mild, moderate, or severe), predictability (expected or unexpected), and potential relationship to the study procedures (definitely related, possibly related, or unrelated). All adverse events are discussed by at least two of the following members of the study team before a consensus is reached: main researcher ([name]), study manager ([name]), and additional medical consultants and experts.

### Adherence assessments

Adherence measures encompass both attendance and compliance of interventions by the randomized participants. Attendance is monitored based on the frequency of sessions participants took part in and is reported as the percent of sessions experienced by each participant, given the total number of scheduled sessions. Compliance, on the other hand, is assessed as the percentage of training sessions performed without significant protocol deviations.

### Data management

All outcome measures are collected through online forms, identified by participant number ID. Each form contains instructions related to standard operating procedures, and a specific researcher is responsible for checking missing or inaccurate data. At the end of each testing day, the same researcher is responsible for creating a backup of the data, which are stored in a cloud system and additionally stored on an external hard drive for security purposes.

### Data monitoring and auditing

The present study does not have a data monitoring committee due to the limited availability of resources. Despite its high value for the overall quality of the study, such a committee would not be mandatory due to the characteristics of the types of interventions and outcomes included in the REPHYCOVE Study.

### Statistical analysis

Analyses will be performed using the SPSS software v. 25.0, adopting an *α* = 0.05. Descriptive data will be presented as means, standard deviations, 95% confidence intervals, or absolute and relative frequencies. Data normality will be tested by the Shapiro–Wilk test, and the Levene test will test the homogeneity of variances. Primary and secondary outcome analyses will be conducted using mixed linear models with “treatment group x timepoint” interaction terms and using baseline values as covariates. An intention-to-treat analysis will include all randomized participants, in which missing data will be imputed using multiple imputations. In contrast, a per-protocol analysis will be performed with only those participants with an attendance rate  ≥ 80%. Effect sizes between-group will be computed based on Cohen’s *d* and the 95% confidence interval.

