## Methods

### Trial design

The REPHYCOVE Study is a randomized, single-blind, parallel, controlled, superiority trial. Participants are randomly allocated in a 1:1 ratio to one of two groups: an intervention group including physical training in combination with cognitive training (PCT) or an active control group including physical training alone (PT). The groups receive supervised training remotely for 12 weeks and are assessed for the primary and secondary outcomes of the study before and after the training period. The present study protocol follows as closely as possible the SPIRIT Statement recommendations [27] and was previously registered in the Clinical Trials database (NCT05309278).

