### Sample size

The sample size calculation was performed using the GPower v. 3.1 software, adopting a significance level of *α* = 0.05 and a power of 80%. Data used in the determination of the effect size *f* for each primary outcome (cognitive capacity: *f* = 0.35; dynamic balance: *f* = 0.22; dual-task performance: *f* = 0.20) were extracted from [16, 29], resulting in a total sample size of 52 participants. To account for possible losses during the study procedures, ten additional participants (i.e., ~ 20%) are to be recruited for the study, totaling 62 participants randomized between the two groups.

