### Outcomes

Primary and secondary outcomes are assessed on three separate days, first at baseline (week 0) and then after the training intervention (week 13). Outcomes are assessed for all randomized participants, irrespective of attendance or completion status. Those who withdraw from the study at any time after randomization are also invited to perform the final study evaluations for inclusion in the intention-to-treat analysis.

The first testing day is held online. Participants answer an anamnesis, and the MMSE and IVCF questionnaires are applied. The second testing day also occurs online. During this session questionnaires related to the self-perceived quality of life, anxiety and depressive symptoms, occupational performance, working memory, and cognitive performance are applied individually by the investigators. Due to the personal nature of the data, assistance to complete the questionnaires is only provided by the investigators if completely necessary. On the third day, participants attend an in-person testing session at the Neuromuscular Assessment Laboratory of the Federal University of Pelotas. Dynamic balance, lower limb strength and endurance, handgrip strength, gait speed, and office blood pressure measures are performed. For all testing sessions, participants are instructed not to perform any intense physical activity 72 h before. Further, post-intervention measures are performed 72 h after the last training session. The temporal description of the study procedures is shown in Table 4.

**Table 4 Tab4:** Temporal description of the study protocol

		**Baseline**		**Intervention**	**Post-intervention**	
**Timepoint**	Week − 1	Week 0 (remotely)	Week 0 (in-person)	Weeks 1–12 (remotely)	Week 13 (remotely)	Week 13 (in-person)

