### Primary outcomes measures

The primary outcomes of this study will focus on changes in cognitive function (as assessed by the MSSE score) and dual-task performance (measured during the TUG test) from baseline to post-intervention. This selection is motivated by the increased fall risk observed in older adults during concurrent tasks, such as walking while engaging in other cognitive or motor activities. Considering that daily life entails a wide range of dual- and multi-tasks, interventions that positively impact cognitive and functional outcomes are imperative for older individuals at a heightened risk of clinical-functional vulnerability [12].

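### With only two assessments, the mixed model uses baseline both as a response and as a covariate, so the group-by-timepoint test is not baseline-adjusted and its validity depends on an unstated covariance structure

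*Protocol article*

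**What the plan says.** The Statistical analysis section of the protocol article gives one model for all primary and secondary outcomes: mixed linear models with group-by-timepoint "interaction terms and using baseline values as covariates". It sets the software and level ("Analyses will be performed using the SPSS software v. 25.0, adopting an *α* = 0.05") and plans multiple imputation for the intention-to-treat analysis. It names no random effect, no covariance structure and no baseline-by-time term.

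Under Trial design, participants are "assessed for the primary and secondary outcomes of the study before and after the training period". The Outcomes section confirms two occasions only, week 0 and week 13. Primary outcomes measures defines the primary outcomes as changes, for example in "dual-task performance (measured during the TUG test) from baseline to post-intervention".

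The Sample size section gives three effect sizes, the smallest being "dual-task performance: *f* = 0.20", "resulting in a total sample size of 52 participants" before the allowance for losses.

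**The concern.** A group-by-timepoint interaction needs at least two levels of time among the responses. With two assessments, one of those levels must be baseline. The sentence then also puts the baseline value on the right-hand side, so one measurement is both outcome and predictor.

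Two things are at stake. First, a reader will take the treatment effect to be baseline-adjusted, with the precision that adjustment brings. Secondly, the model is misspecified for the baseline rows, because the covariate explains them almost by construction. Depending on how the within-person covariance is handled, this can distort the standard error or leave no valid fit. The sentence governs every primary and secondary result of the trial.

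**Working it through.** **Inputs.** From the protocol: two timepoints, 1:1 allocation, α = 0.05, 80% power, f = 0.35, 0.22 and 0.20, N = 52 before losses and 62 after. Assumed, because the protocol does not give them: baseline to week-13 correlation ρ (range 0.3 to 0.8), equal variances (set to 1) and complete data. n is the number per arm.

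**1. The plan's own figure.** For the two-group, two-timepoint interaction the noncentrality is λ = f²·N·2/(1−ρ). With f = 0.20, N = 52 and ρ = 0.5, λ = 0.04 × 52 × 2 / 0.5 = 8.32. On 1 and 50 degrees of freedom the power is 0.807. The same calculation needs 44 participants for f = 0.22 and 20 for f = 0.35, so 0.20 sets the size, and 52 + 10 = 62. The figure reproduces as an interaction test without a covariate, if ρ = 0.5. (A between-groups test at f = 0.35 also gives 52, but would need 124 and 150 for the other two outcomes.) An f of 0.20 corresponds to a difference in change of 4 × 0.20 = 0.8 SD. Check: 0.8² / [4(1−0.5)/26] = 8.32.

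**2. The covariate cancels.** The baseline covariate takes the same value in both rows of a participant. In the contrast (week 13 minus baseline) between arms it subtracts out, whatever its coefficient. In 20,000 simulated null trials per setting, the interaction estimate equalled the raw difference in mean change every time. The planned imputation completes the data, so this carries over to each imputed intention-to-treat data set.

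**3. The standard error, by covariance structure.** The pooled slope on baseline is (1+ρ)/2. The residuals are (1−ρ)/2 × y₀ at baseline and y₁ − (1+ρ)/2 × y₀ at week 13. Their covariance is (1−ρ)/2 × [ρ − (1+ρ)/2] = −(1−ρ)²/4, which is always negative.

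- *Random participant intercept.* A variance cannot be negative, so it is truncated to zero. The pooled residual variance is (1−ρ)(3+ρ)/4, and the model variance of the interaction is (1−ρ)(3+ρ)/n. The true variance is 4(1−ρ)/n. The ratio is (3+ρ)/4, or √[(3+ρ)/4] for the standard error.
- *Exchangeable covariance that may be negative.* The standard error returns to that of the change score. In one simulated data set with ρ = 0.5 it was 0.282, against 0.280 without the covariate and 0.259 with a random intercept.
- *Separate baseline variance, for example unstructured.* A slope of 1 fits the baseline rows exactly, their residual variance goes to 0, the likelihood is unbounded and there is no valid fit.

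**4. Size under a random intercept** (20,000 null trials per cell):

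| ρ | SE ratio √[(3+ρ)/4] | Type I error, N = 52 | Type I error, N = 62 |
|---|---|---|---|
| 0.3 | 0.908 | 7.5% | 7.5% |
| 0.5 | 0.935 | 6.8% | 6.6% |
| 0.7 | 0.962 | 5.9% | 5.9% |
| 0.8 | 0.975 | 5.7% | 6.0% |

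These use the residual degrees of freedom of the pooled rows. With N − 2 instead, the N = 52 figures are 7.2%, 6.5%, 5.6% and 5.4%. In the same trials ANCOVA of week 13 on baseline rejected in 4.8% to 5.2%, and the change-score test (no covariate) in 4.7% to 5.2%.

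**5. What adjustment would bring.** The ANCOVA variance is 2(1−ρ²)/n. Divided by 4(1−ρ)/n this is (1+ρ)/2, which is 0.75 at ρ = 0.5. For the 0.8 SD effect at N = 52:

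| ρ | Power, change score | Power, ANCOVA |
|---|---|---|
| 0.3 | 0.667 | 0.842 |
| 0.5 | 0.807 | 0.904 |
| 0.7 | 0.955 | 0.977 |
| 0.8 | 0.994 | 0.997 |

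**The case against.** The strongest reply is that the article states no random intercept. Covariance detail is commonly left to an analysis plan that is not shown, and under one admissible structure the standard error is correct. This stands. A reader might infer that type I error exceeds 5% for every result. The document does not support that: the inflation follows only with a random intercept, it is modest, and its size depends on a correlation that the protocol does not give.

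It can also be said that the unadjusted difference in change is unbiased under randomisation, matches the definition of the primary outcomes as changes, and is what 52 participants were sized for. This stands too. The lost precision is a missed gain, not a shortfall against the plan, and no error in the sample size follows.

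A benign reading is that baseline was meant only as a covariate and the interaction is a slip. Timepoint then has a single level and the stated interaction cannot be estimated, so the sentence still needs correction.

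The reply does not remove the core. The point is not that a covariance structure is missing. The sentence combines two terms that do not fit a two-visit design, and no covariance choice makes the interaction the baseline-adjusted effect.

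**Conclusion.** The point holds. As written, baseline is both a response and a covariate, and with complete data the interaction test is the unadjusted difference in change. That part rests only on the text and on algebra.

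The consequence for inference is conditional:

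- With a random participant intercept, the standard error is about 2% to 9% too small and type I error is about 5.7% to 7.5%, for ρ from 0.8 to 0.3.
- With a separate baseline variance, the model has no valid fit.
- With an exchangeable covariance allowed to be negative, inference is correct and the covariate does nothing for the treatment test.

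The figures assume equal variances and complete data. The rise in power from about 81% to 90% further assumes ρ = 0.5 and the effect implied by f = 0.20.

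**What to change.** Use baseline once. Preferred replacement for the model sentence:

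> Each outcome at week 13 is analysed by ANCOVA with group, the baseline value of that outcome and, for outcomes other than MMSE, baseline MMSE (the stratification variable); the group coefficient with its 95% CI is the treatment effect.

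The exception for MMSE matters: it is itself a primary outcome, and without the exception its baseline would enter twice.

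Also valid is a two-timepoint mixed model with baseline as a response and no baseline covariate of the same outcome, in one of two forms:

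- Baseline means constrained equal across arms. Efficiency is similar to ANCOVA, and the model also gives the within-group changes that the hypothesis mentions.
- Baseline means unconstrained. This is the change-score test and matches the sample-size basis if ρ = 0.5.

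The cost is one sentence. It needs no new data and no change to the 62 participants, and it works with the planned multiple imputation. It should be settled before anyone sees results by arm, so that the choice between models is not made from the data.

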### Ethics and dissemination

#### Ethics approval and consent to participate

The study protocol was approved by the Universidade Federal de Pelotas Ethics Review Board (n. 5.471.834). Specific COVID-19 safety protocols are being followed based on the [21]. Individuals are informed about all procedures related to the study participation, including possible risks and benefits, and sign an online informed consent form on the Google Forms platform. The responsible researcher ([name]) is available to answer any questions related to the procedures as needed. If necessary, amendments to the study protocol will be communicated to the Ethics Review Board, and our research team will update the protocol of the clinical trial registry accordingly.

#### Confidentiality

Participants’ identities are preserved, and their respective data are identified using individual identifying numbers (ID).

#### Dissemination policy

Upon completion of the study, our dissemination plan aims to circulate the study’s results to as many interested parties as possible. First, participants will receive individualized reports with their results in a language comprehensible to the lay public. Participants will also receive general guidance on how to maintain the practice of physical and cognitive exercises, as well as information on successful aging and general health care. Additionally, the study’s main findings will also be published in the press for the general public. Finally, scientific dissemination will be achieved through the publication of research manuscripts and posters and/or oral presentations at scientific events.

## Discussion

According to the 2022 World Population Prospects [57], it is estimated that by 2050 one in every six people in the world will be over 65 years old, compared to one in every ten individuals in 2022. As a consequence of this, our society will undergo a comprehensive demographic transition. Thus, it is not only essential to understand how the aging process happens but also how one can intervene to improve longevity and the health span of this already considerable portion of the world’s population. To achieve this goal, access to non-pharmacological strategies such as physical and cognitive exercise training will be of absolute importance [34].

The COVID-19 pandemic, which began in 2019, directly and indirectly affected the health of millions of people around the globe [9]. Several reports indicate that the lockdown measures taken to contain the spread of the virus, although necessary, negatively impacted the physical and cognitive well-being of many of these individuals [8, 49]. In older people who were followed from December 2020 until August 2021, a significant decline in physical and cognitive function, and a worsening in self-perceived quality of life and the incidence of depressive symptoms was observed [9]. As a consequence, this population not only had to deal with aspects related to aging, but also with negative aspects associated with the pandemic.

The regular practice of physical exercises has been shown as a key factor towards the maintenance of older adults’ functional capacity, physical fitness, strength, agility, balance, muscle quality, cognitive capacity, quality of life, reduction of depressive symptoms, and independence in carrying out activities of daily activities [25, 26, 31, 47]. The combination of such an exercise program with the regular practice of cognitive exercises has been further shown as relevant for those at an increased risk of frailty. Specifically, improvements in physical and cognitive domains have been observed, such as self-perceived quality of life, gait speed, strength, balance, global cognitive function, verbal fluency, memory, executive function, inhibitory control, mood, among others [4, 30, 45, 50].

Remote exercise emerges as a relevant tool for situations where individuals cannot attend in-person activities. Even in people with Parkinson’s disease, remote training has been shown as a safe and feasible alternative to implementing complex training programs [53], with only 11 adverse events being reported in response to 6 months of intervention in 130 participants, seven in the intervention group, and four in the active control group. Similar results were also observed in older adults and in fibromyalgia patients [3, 22]. Overall, these studies demonstrate the effectiveness of remote training intervention for older and at risk populations. They also corroborate the aims of the present study and especially the importance of staying active during situations of social isolation or when some other aspect prevents the performance of in-person exercise (e.g., physical frailty or functional impairments) [6, 11, 17]. Within this context, the present study seeks to take the understanding of remote exercise one step further by combining the established effectiveness of remote physical exercise with the inclusion of a remote cognitive exercise training portion as well, which remains poorly understood.

